### Interventions

Aspirin enteric-coated tablets (100 mg, QD) (Bayer Healthcare Co. Ltd.): an anti-platelet medicine widely used in the treatment for cardiovascular disease.Salvianolate injection (200 mg + 5% glucose injection 250 mL, i.v.) (Shanghai Green Valley Pharmaceutical Co. Ltd.): the main ingredient of the salvianolate injection is salvianolic acid B (SAB), which is extracted from the root of red salvia. Red salvia is used in TCM for promoting blood circulation to counter blood stasis, which is clinically effective in the treatment for cardiovascular disease.

The detail of dose and duration of the medication is illustrated in Table 1.

**Table 1 Tab1:** Dose and duration of medication

Group	Medication	Dose and method	Duration (days)
Aspirin group	Aspirin	100 mg QD, oral	10
Salvianolate group	Salvianolate	200 mg + 5% glucose 250 mL, i.v. injection	10
Experimental group	Salvianolate + aspirin	100 mg QD oral aspirin and 200 mg + 5% glucose 250 mL i.v. salvianolate injection	10

### Combination

Participants are not allowed to take any kind of TCM or western medicine with pharmacological effects of activating blood circulation, platelet aggregation, and anti-coagulation or belonging to the non-steroidal anti-inflammatory class.In case of angina pectoris, participants can take isosorbide mononitrate after approval by researchers. It is permitted to take other medicines that are not metabolized through aspirin esterase and catechins-O-methyl transferase (COMT) and the record the combination.

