### Aspirin

Aspirin is among the most commonly used drugs worldwide. Its widespread use is attributed to the high prevalence of ischemic heart disease and cerebrovascular accidents, along with its proven efficacy in preventing them. Clinical trials show that antiplatelet therapy with aspirin reduces the risk of myocardial infarction, stroke, and vascular death. Aspirin can prevent platelet aggregation because it leads to decreased thromboxane A2 (TXA2) through the inhibition of cyclooxygenase (COX) combined with removed acetyl [4, 5]. The whole process deacetylates by several kinds of esterase in digestive juice and blood after oral administration. Therefore, the curative effect of aspirin may rely on its deacetylation rate in the human body. Aspirin’s curative effect may decline if it hydrolyzes too rapidly in the digestive juice and blood [6].

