## Objectives

The primary objective of this study is to determine the influence of salvianolate on the activity of aspirin esterase and that of aspirin on the activity of salvianolate metabolic enzyme.

The secondary objective is to determine the PK-PD characteristics of the salvianolate and aspirin combination and analyze the correlation between the exposure level and pharmacodynamic index of the medicines.

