### Randomization

This is a single-center clinical trial of three groups. The sample size is 18 and all participants will be distributed 1:1:1. The randomization code will be developed by the study statistician. The trial cases were divided into three processing groups. The random numbers of “trial cases” was produced by SAS random procedure: they were arranged vertically by block and randomly coded. The randomized coding of test cases was the same as that of the experimental medicine. When a participant has been enrolled, the research pharmacy will randomize the individual based on the master randomization list.

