## Proposed trial outcome measures

### Primary outcome

Change in aspirin esterase activity at different blood concentrations: biological analysis will be conducted by liquid chromatography tandem mass spectrometry (LC-MS/MS) to detect aspirin and salicylic aspirin and salicylic acid: CSA/C(ASA + SA). (Time frame: blood samples are acquired before aspirin administration on days 8 and 9. On day 10, blood samples are acquired before and after aspirin administration at 5 min, 15 min, 30 min, 45 min, 1 h, 2 h, 4 h, 8 h, 12 h, and 24 h.)Change in COMT activity at different blood concentrations: COMT activity is the main metabolic enzymes of SAB. A kit was used to detect COMT activity. (Time frame: blood samples are collected before injection on days 8 and 9. On day 10, blood samples are collected before and after injection at 5 min, 15 min, 30 min, 45 min, 1 h, 2 h, 4 h, 8 h, 12 h, and 24 h.)

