### PK index

#### Aspirin esterase activity

Using data from the blood sample analysis (CSA/C(ASA + SA)), we will compare the results of the three arms by ANOVA analysis.

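### The rule on permitted co-medication tests whether the two enzymes metabolise a drug, not whether the drug alters their activity, which is what both primary outcomes measure

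*Protocol article*

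**What the plan says.** The primary objective (Objectives) is to "determine the influence of salvianolate on the activity of aspirin esterase and that of aspirin on the activity of salvianolate metabolic enzyme". The two primary outcomes match it: "Change in aspirin esterase activity at different blood concentrations", taken from the share of salicylic acid in aspirin plus salicylic acid, and "Change in COMT activity at different blood concentrations", measured with a kit.

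The Combination section does three things about other medicines:

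- It bars those "with pharmacological effects of activating blood circulation, platelet aggregation, and anti-coagulation or belonging to the non-steroidal anti-inflammatory class".
- It allows isosorbide mononitrate for angina with the researchers' approval.
- It opens the door to the rest on one condition, with use to be recorded: "It is permitted to take other medicines that are not metabolized through aspirin esterase and catechins-O-methyl transferase (COMT").

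The Withdrawal section separately provides that patients whose other medication affects the results are taken out. It gives no criterion for which medicines these are.

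On size and analysis, "The sample size is 18 and all participants will be distributed 1:1:1" (Randomization), and for the esterase outcome "we will compare the results of the three arms by ANOVA analysis". COMT activity is also compared across arms by ANOVA.

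**The concern.** Being a substrate of an enzyme and changing its activity are different properties. A drug can inhibit or induce an enzyme without being metabolised by it. The trial asks about activity, but its permission rule asks about metabolism. The rule does keep out competing substrates. It lets through a non-substrate inhibitor or inducer, which acts on the measured quantity itself.

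Two things are at stake. First, a difference between arms that comes from a background medicine could be read as a salvianolate–aspirin interaction, or could hide one. Second, the Combination and Withdrawal sections give different answers for the same medicine: the first permits it by metabolic route, and the second removes the patient by effect on the result. In an open-label trial with arms of 6, an undefined reason for withdrawal after randomisation is undesirable.

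**Working it through.** **The sections side by side.** Take a hypothetical medicine that lowers COMT or esterase activity, is metabolised by neither, and has no circulatory, platelet, anticoagulant or anti-inflammatory action.

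- Study participants: no criterion concerns medication other than the study drugs. Only the general investigator-judgement exclusion could apply.
- Combination, prohibited classes: not caught.
- Combination, permission rule: passes, and is recorded.
- Primary outcome: directly affected.
- Withdrawal: the patient may be removed, but only after use and with no stated test.

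So the rule admits a medicine that the primary outcomes cannot tolerate, and the only provision that looks at effect on the result acts too late.

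**Can the described design absorb it?** The Sample collection section places the first sample before dosing on day 8. The text describes no untreated value against which a patient's altered activity could be corrected. Randomization describes blocks but no stratification by medication. The analysis sections state ANOVA across arms, with no use of the medication record.

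**Scale.** Inputs: 18 participants, 1:1:1 (Randomization), so n = 18/3 = 6 per arm. Let d be the shift in a patient's outcome caused by the medicine. The documents give no value for d.

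- Shift in the arm mean with k such patients: k·d/6. One patient gives d/6 (about 17% of d), and two in the same arm give d/3.
- Added within-arm sum of squares from one such patient, if d is unrelated to the patient's underlying value: d²(1 − 1/6) = 5d²/6. On 5 degrees of freedom, the expected variance of that arm rises by d²/6. Pooled over three arms (15 degrees of freedom) it rises by (5d²/6)/15 = d²/18.
- If the patient is instead withdrawn and not analysed, the arm falls from 6 to 5 and the standard error of its mean rises by √(6/5) = 1.095, about 10% for the same SD.

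The contrast between arms moves and the error term grows at the same time. The plan states no effect size or SD to compare these with, so they cannot be turned into a false-positive rate or a loss of power.

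**The case against.** The strongest reply is that the document does look at effect on the result, in the Withdrawal section. In addition, permitted medicines are recorded and the investigator may exclude unsuitable patients. This stands in part: the rule is not the only safeguard. But the withdrawal provision has no criterion, works only after use, and contradicts the permission given in Combination.

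Several stronger readings are tempting but unsupported.

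- *Systematic bias.* A reader might infer that the primary comparison is confounded. For medicines in use at randomisation, use is unrelated to arm in expectation. What remains is chance imbalance in arms of 6 and extra variance, part of which ANOVA counts in its error term.
- *A known size.* Assuming a 30–80% fall in activity would give a shift in the arm mean of 0.3/6 = 5% to 0.8/6 = 13% for one patient, and 10% to 27% for two. Nothing in the documents supports that range. It also does not carry over to the esterase outcome, a ratio that cannot exceed 1 and need not move in proportion to the hydrolysis rate.
- *Expected use.* The background section on salvianolate injection says it is widely combined with other cardiac medicines, so some co-medication is plausible. No document says that any of these alters either enzyme.
- *A missing washout.* A reader might ask for a window before day 1. An article commonly leaves this to the full protocol, and the first sample is on day 8, at least seven days after dosing starts.
- *A faulty enzyme label.* The Aspirin section says "The whole process deacetylates by several kinds of esterase in digestive juice and blood after oral administration". The ratio reflects net hydrolysis, so aspirin esterase serves as a collective name. This affects only how the corrected test should be worded.

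**Conclusion.** The concern holds as a gap in a stated rule. The Combination section permits by substrate status, the primary outcomes measure activity, and a non-substrate inhibitor or inducer therefore falls on the permitted side. The section also conflicts with Withdrawal over the same medicine.

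The effect is d/6 on an arm mean per affected patient, with added variance, where d is unknown. Whether it matters in practice depends on such medicines being taken and falling unevenly across arms, which the documents neither show nor rule out. The conclusion itself rests only on the distinction between substrate and modifier and on the wording of the sections compared above. An unseen full protocol may hold a more detailed list, but the rule as published tests the wrong property for its own endpoints.

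**What to change.** Reconcile Combination with Objectives, Primary outcome and Withdrawal. The co-medication test should cover known effect on the activity of COMT or of the esterases that hydrolyse aspirin, as well as substrate status. It should be applied at eligibility, so that the question is settled before randomisation, and Withdrawal should refer to the same test so that a permitted medicine cannot also be a reason for removal.

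This is a matter of valid measurement. It names no medicine and leaves the isosorbide mononitrate allowance alone. It does not ask that background treatment be held constant, which would be a clinical rule and would sit badly with that allowance.

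The cost is a change of wording in two sections, a matching eligibility check and a review of each medication history. A few patients may be screened out.

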### Randomization

This is a single-center clinical trial of three groups. The sample size is 18 and all participants will be distributed 1:1:1. The randomization code will be developed by the study statistician. The trial cases were divided into three processing groups. The random numbers of “trial cases” was produced by SAS random procedure: they were arranged vertically by block and randomly coded. The randomized coding of test cases was the same as that of the experimental medicine. When a participant has been enrolled, the research pharmacy will randomize the individual based on the master randomization list.

### Sample collection

Blood sampling will be conducted in three groups:First group (aspirin group) sampling processThe participants will take aspirin before breakfast for 10 consecutive days. Blood samples will be collected before aspirin administration on days 8 and 9. After the participants take aspirin on an empty stomach on the morning of day 10, blood samples will be collected from the elbow vein before administration and at 5 min, 15 min, 30 min, 45 min, 1 h, 2 h, 4 h, 8 h, 12 h, and 24 h after administration. The participants should maintain a half-berth for 2 h during non-blood sampling time, during which they will be monitored for blood pressure and heart rate.Second group (salvianolate group) sampling processThe participants will receive salvianolate injection in the emergency room of Xiyuan Hospital after a meal for 10 consecutive days. Blood samples will be collected before administration on days 8 and 9. The participants will be injected with salvianolate on an empty stomach on the morning of day 10. The injections will be dropped by 1.5 h ± 15 min. Blood samples will be collected from the elbow vein before injection and at 5 min, 15 min, 30 min, 45 min, 1 h, 2 h, 4 h, 8 h, 12 h, and 24 h after administration. The participants should maintain a half-berth for 2 h during non-blood sampling time, during which they will be monitored for blood pressure and heart rate.Third group (experimental group) sampling processThe participants take aspirin before breakfast followed by salvianolate injection in the emergency room of Xiyuan Hospital after a meal for 10 consecutive days. Blood samples will be collected before administration on days 8 and 9. Salvianolate will be injected on an empty stomach on the morning of day 10, 2 min after which the participants will take aspirin with 200 mL warm water. The injections will be dropped by 1.5 h ± 15 min. The blood samples will be collected from the elbow vein before administration and at 5 min, 15 min, 30 min, 45 min, 1 h, 2 h, 4 h, 8 h, 12 h, and 24 h after administration. The participants will be able to maintain a half-berth for 2 h during non-blood sampling time, during which they will be monitored for blood pressure and heart rate.

## Proposed trial outcome measures

### Primary outcome

Change in aspirin esterase activity at different blood concentrations: biological analysis will be conducted by liquid chromatography tandem mass spectrometry (LC-MS/MS) to detect aspirin and salicylic aspirin and salicylic acid: CSA/C(ASA + SA). (Time frame: blood samples are acquired before aspirin administration on days 8 and 9. On day 10, blood samples are acquired before and after aspirin administration at 5 min, 15 min, 30 min, 45 min, 1 h, 2 h, 4 h, 8 h, 12 h, and 24 h.)Change in COMT activity at different blood concentrations: COMT activity is the main metabolic enzymes of SAB. A kit was used to detect COMT activity. (Time frame: blood samples are collected before injection on days 8 and 9. On day 10, blood samples are collected before and after injection at 5 min, 15 min, 30 min, 45 min, 1 h, 2 h, 4 h, 8 h, 12 h, and 24 h.)

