### Why is this study needed now?

Traditional Chinese medicine (TCM) has a long history of usage in China and is also widely used as alternative medicine worldwide [16, 17]. A survey shows that approximately 1.5 million adults in the United States use one or more kinds of herbal medicine while regularly taking prescription medications [18]. Meanwhile, several clinics in the UK use TCM. However, it is unclear whether drug–drug interaction (DDI) mechanisms between TCM and western medicine limit the application of TCM [19, 20]. Therefore, it is necessary to determine the DDI between TCM and western medicine. DDI can be divided into three groups: pharmacokinetics DDI; pharmacodynamics DDI; and in vitro DDI. Pharmacokinetics DDI generally involves the interaction of drugs in the process of absorption, distribution, metabolism, and excretion. TCM, which contains many bioactive ingredients, may engage in a synergistic or antagonistic interaction with other medicines. In this study, we focus on pharmacokinetics DDI between salvianolate and aspirin. Through the establishment of the PK-PD model, we aim to evaluate the relationship between the change of pharmacokinetics and therapeutic effect index in the combined use of salvianolate and aspirin. Finally, we discuss the possible mechanism of medicine combination in the treatment for CHD and provide an experimental basis for a clinically rational medicine combination.

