## Discussion

A combination of salvianolate and aspirin may provide an effective and safe therapeutic option for patients with CHD; however, its DDI mechanism remains unclear. We investigate this inquiry by applying a PK-PD model. Research and clinical practice become intimately intertwined on the ground of PK-PD trials. We apply typical research instruments (e.g. randomization, control) to achieve the ultimate clinical objective, to reliably and empirically determine the best therapeutic choice for patients, and also meet the aims of innovative and timely research. This study establishes a PK-PD model to determine the PK-PD characteristics of the salvianolate and aspirin combination and analyze the correlation between exposure level and pharmacodynamic index of the medicines.

Metabolic enzymes play an important role in pharmacokinetics DDI. The main metabolic enzyme is CYP450, which is essential for the metabolism of many drugs. According to statistics, CYP450 isoforms are responsible for the oxidative metabolism of approximately 85% of the marketed drugs [22]. However, neither aspirin nor salvianolate injection has any relation with CYP450. Aspirin is hydrolyzed by several kinds of esterases [23–25] and the main active component of salvianolate, SAB, is metabolized by COMT. These enzymes might be the key point of pharmacokinetics DDI between aspirin and salvianolate injection. In this case, we plan to use ELISA to measure the activity of COMT and a formula containing aspirin and its metabolite, salicylic acid, to evaluate the activity of esterase. In summary, we analyze the pharmacokinetics DDI of salvianolate and aspirin through COMT and esterase, respectively, to determine the influence between the metabolic processes of each medicine. This research also explores the functional mechanism of the two medicines on the treatment of CHD. It is the trend to establish PK-PD based on functional mechanism. The function of salvianolate and aspirin is related to the inhibition of platelet aggregation and blood coagulation. Thus, we choose P-selection, PAC-1, and P2Y12 acceptor and PDE enzymes as efficacy indexes to explore their correlation with drug concentration.

Ultimately, this research, in its entirety, will provide an approach of filling the gap between science and practice, supplying evidence of DDI, and facilitating the use of medicine combination in the treatment of CHD.

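### The primary 'aspirin esterase activity' is a plasma metabolic ratio that moves without any enzyme change, so it supports conclusions about exposure and apparent hydrolysis, not measured esterase activity

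*Protocol article*

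**What the plan says.** The primary objective (Objectives) includes to "determine the influence of salvianolate on the activity of aspirin esterase". The matching outcome (Primary outcome) is "Change in aspirin esterase activity at different blood concentrations". It is obtained by measuring aspirin (ASA) and salicylic acid (SA) by LC-MS/MS and forming CSA/C(ASA + SA), before dosing on days 8, 9 and 10 and from 5 min to 24 h after the day-10 dose. The Discussion confirms the substitution: the plan uses "a formula containing aspirin and its metabolite, salicylic acid, to evaluate the activity of esterase". For the other primary enzyme the Primary outcome section says "A kit was used to detect COMT activity"; no such assay is described for esterase. The Statistical analysis plan section compares the ratio between arms by ANOVA.

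Three other statements bear on how the ratio behaves. The tablet is enteric-coated (Interventions). Aspirin "deacetylates by several kinds of esterase in digestive juice and blood after oral administration" (Background, Aspirin). And "Pharmacokinetics DDI generally involves the interaction of drugs in the process of absorption, distribution, metabolism, and excretion" (Why is this study needed now?).

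**The concern.** The objective names an enzyme activity; the measurement is a ratio of two plasma concentrations after an oral dose. The ratio depends on how fast aspirin enters blood, how much of it arrives intact and how fast salicylate leaves, as well as on how fast esterase works.

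Two readings are at risk. Within a patient, a ratio that changes across the concentration–time curve would be reported as esterase activity changing with concentration, although such change arises with a constant enzyme. Between arms, a difference would be reported as an effect of salvianolate on esterase, although other routes could produce it. Conversely, variation in tablet release time could hide a modest real effect.

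**Working it through.** **Inputs from the article.** The formula and sampling times (Primary outcome); an enteric-coated tablet (Interventions); hydrolysis both before and after entry to blood (Background, Aspirin); 18 participants allocated 1:1:1 (Randomization), so 18/3 = 6 per arm. The article states no figure for the ratio that could be reproduced.

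**Assumptions (the article gives no pharmacokinetic values).** A linear model in molar units with equal volumes, ten daily doses, and all aspirin converted to salicylate.
- Set A: aspirin half-life 20 min, salicylate half-life 2.5 h, half of the absorbed aspirin hydrolysed before reaching blood (intact fraction F = 0.5), absorption 1.5/h after release.
- Set B, for range: aspirin half-life 0.3 h, salicylate 3 h (2 to 4.5 h), presystemic loss 0.5 (0.3 to 0.7), absorption 1.5/h (0.5 to 4/h), lag 0 to 4 h.

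Write R = SA/(ASA + SA).

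**1. R is tied to the concentrations by construction.** dR/dASA = −SA/(ASA + SA)², which is negative. R falls when aspirin rises, whatever the enzyme does.

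**2. Time since dose, esterase constant, no lag.** Set A: R is about 0.55 at 5 min, 0.815 at 1 h, 0.936 at 2 h and 1.00 from 8 h. Set B: 0.56, 0.84, 0.95 and 1.00. With a 2 h lag, every sample up to and including 2 h reads 1.00, because only salicylate left from earlier doses is present.

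**3. Release time.** Set A, lag uniform over 1–4 h, esterase identical in everyone:

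| Sample | SD of R from lag alone | Shift for a 30% fall in esterase | Standard error of a 6 v 6 difference from lag alone |
|---|---|---|---|
| 2 h | 0.16 | 0.015 | 0.16 × √(2/6) = 0.092 |
| 4 h | 0.13 | 0.045 | 0.13 × √(2/6) = 0.075 |

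At either time the standard error from lag alone exceeds the shift.

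**4. Intact fraction.** Set B, 1 h: R = 0.775 with 30% presystemic loss, 0.837 with 50% and 0.901 with 70%. Halving the total amount absorbed, with presystemic loss unchanged, leaves R unchanged at every time. Bioavailability therefore matters only through the fraction reaching blood intact.

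**5. Salicylate elimination, early samples.** Set A, time after release:

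| Time | Base | Esterase × 0.7 | Salicylate clearance ÷ 0.7 | Ratio of the two shifts |
|---|---|---|---|---|
| 0.5 h | 0.695 | 0.646 | 0.688 | 0.007/0.049, about 1/7 |
| 1 h | 0.815 | 0.754 | 0.806 | 0.009/0.061, about 1/7 |
| 2 h | 0.936 | 0.889 | 0.927 | 0.009/0.047, about 1/5 |

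**6. AUC form.** With D the amount absorbed, AUC_ASA = F × D/CL_esterase and AUC_SA = D/CL_SA, so AUC_SA/AUC_ASA = CL_esterase/(F × CL_SA). Set A: CL_esterase/CL_SA = 150 min/20 min = 7.5, and 7.5/0.5 = 15.0. Esterase × 0.7, salicylate clearance ÷ 0.7 and F ÷ 0.7 each give 15.0 × 0.7 = 10.5. In this form the three causes cannot be told apart.

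**The case against.** The strongest reply is that arms are randomised and sampled at matched times. Release lag and patient differences in clearance are then noise, not bias, unless salvianolate itself alters them. Salvianolate is given intravenously, and the article lists absorption and excretion only as general interaction routes, not as known effects of this product. This stands. A reader might infer that the arm difference says nothing about esterase; the documents do not support that. The difference is informative on a condition that the ratio alone cannot verify. On day 10 only the combination arm has the concurrent infusion, and taking the tablet with 200 mL of water is stated only for that arm (Sample collection), though this may be an effect of condensing.

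A reader might also infer that esterase, salicylate clearance and presystemic loss give the same index throughout. That holds for the AUC ratio, which the article does not define as the outcome. In early samples the salicylate-clearance effect is only one fifth to one seventh of the esterase effect.

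The presystemic route is also partly on target: the article attributes hydrolysis in digestive juice to esterases as well, and its objective does not say blood esterase.

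Finally, aspirin and salicylic acid are each measured and PK-PD modelling is planned, so the data can already separate salicylate clearance from hydrolysis. This too stands, and it shapes the remedy.

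**Conclusion.** The concern holds in a bounded form. The article equates a metabolic ratio with enzyme activity, and with constant esterase that ratio spans about 0.55 to 1.00 over the sampling times. Its within-patient change across concentrations is not evidence of enzyme change. A randomised arm difference supports an esterase effect only if salvianolate leaves release, presystemic loss and salicylate elimination unchanged. Otherwise release lag is noise, but enough to swamp a modest effect: SD about 0.16 and 0.13 against shifts of about 0.015 and 0.045 at 2 h and 4 h.

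The sizes rest on assumed half-lives, absorption and lag. The sign in step 1 needs no such values, and the identity in step 6 needs only the linear model. A reader might want a single power or false-attribution figure. None can be given, because the article does not say which summary of the ratio enters the ANOVA, and different summaries behave differently.

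**What to change.** 1. In Objectives, Primary outcome and Discussion, relabel CSA/C(ASA + SA) as a descriptive salicylate metabolic ratio, and state that its within-patient change across concentrations is not read as enzyme change.
2. Compare aspirin AUC and salicylic acid AUC separately between the aspirin and combination arms, from the LC-MS/MS data already planned. In a linear model aspirin AUC responds to hydrolysis and to the intact fraction but not to salicylate clearance; salicylic acid AUC responds to salicylate clearance but not to esterase. Both scale with the amount absorbed, so they should be read together.
3. Limit the primary conclusion to exposure and apparent hydrolysis, with no claim of measured esterase activity.
4. Optional: an ex vivo assay incubating blood with a fixed amount of aspirin and measuring the salicylic acid formed. The article gives no sample volumes or handling, so feasibility on existing samples must be checked. It would be a new assay after recruitment began (Trial status: April 2018), and it covers blood esterase only.

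Items 1 to 3 cost protocol wording and an analysis of existing measurements. The downside is a narrower primary conclusion. Aspirin AUC also inherits the wide sampling gaps at 2, 4 and 8 h if release is late.

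### The primary esterase index, a per-sample SA/(ASA+SA) ratio after an enteric-coated tablet, depends strongly on time since absorption as well as on enzyme activity, and the draw times make this worse

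*Protocol article*

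**What the plan says.** All references are to the protocol article.

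- **Aim.** Objectives: "determine the influence of salvianolate on the activity of aspirin esterase", alongside the effect of aspirin on the enzyme that metabolises salvianolate.
- **Index.** Primary outcome gives the outcome as "Change in aspirin esterase activity at different blood concentrations" and its measurement as "detect aspirin and salicylic aspirin and salicylic acid: CSA/C(ASA + SA". The Discussion calls this "a formula containing aspirin and its metabolite, salicylic acid, to evaluate the activity of esterase". COMT, the other primary enzyme, has its own assay kit; esterase has only the ratio.
- **Formulation.** Interventions: "Aspirin enteric-coated tablets (100 mg, QD".
- **Draws.** Before dosing, "blood samples are acquired before aspirin administration on days 8 and 9" and again on day 10; then "after aspirin administration at 5 min, 15 min, 30 min, 45 min, 1 h, 2 h, 4 h, 8 h, 12 h, and 24 h".
- **Analysis.** Aspirin esterase activity: "Using data from the blood sample analysis (CSA/C(ASA + SA)), we will compare the results of the three arms by ANOVA analysis".
- **Size.** Randomization: 18 participants allocated 1:1:1, so 6 per arm.

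The article names no exposure measure (AUC), no adjustment for absorption time and no direct esterase assay.

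**The concern.** ASA turns into SA from the moment it is absorbed, and partly before. The share of SA in a sample therefore rises with the age of the absorbed dose even if the enzyme never changes. An enteric coat delays release by an amount that differs between patients, so one clock time stands for a different dose age in each patient. Samples that contain no ASA say nothing about the enzyme, and this schedule can put many draws there.

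The primary esterase comparison is at stake. With 6 patients per arm, scatter from absorption time and readings at the ceiling can bury a real interaction, and a null result could then be read as evidence of none. There is a second, conditional issue: if the blood concentrations named in the outcome are those of ASA or SA, the index contains the quantity it is set against.

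**Working it through.** **Inputs from the article.** Ratio R = SA/(ASA+SA); enteric-coated tablet; 10 post-dose and 3 pre-dose draws; 6 per arm. The article gives no alpha, power, effect size or SD, so it has no figure of its own to reproduce beyond 18/3 = 6.

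**Assumed inputs (not in the article).** Absorption lag 0 to 6 h; ASA half-life 20 min (range 14 to 28); SA half-life 3 h; fraction hydrolysed before the circulation f = 0.5; equal volumes; daily dosing for 10 days. The absorption rate ka is 1.5/h in steps 3 to 5 and 2/h in step 7.

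**1. Draws.** Five of 10 post-dose draws (50%) are at or before 1 h. That is 5 of 11 on day 10 (45%) and 5 of 13 overall (38%). The rest are at 2, 4, 8, 12 and 24 h.

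**2. Algebra.** R = 1 − ASA/(ASA+SA). If ASA = 0 and SA > 0, then R = 1 whatever the enzyme does. If both are below quantification, R is undefined.

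**3. Same enzyme, different lag.** With x = t − lag, ke = ln2/0.333 = 2.08/h and dose 1:

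ASA(x) = (1−f)·ka/(ka−ke)·[exp(−ke·x) − exp(−ka·x)]

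SA gains f of the absorbed dose plus ke·ASA and is lost at ks = ln2/3 = 0.231/h. Example at 1 h without lag: ASA = 0.75/(−0.579) × (0.125 − 0.223) = 0.127. ASA+SA is 0.705, so R = 1 − 0.127/0.705 = 0.82.

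| Lag (h) | R at 1 h | R at 2 h | R at 4 h | R at 8 h |
|---|---|---|---|---|
| 0 | 0.82 | 0.94 | 0.99 | 1.00 |
| 0.5 | 0.70 | 0.89 | 0.99 | 1.00 |
| 1 | 1.00 | 0.82 | 0.98 | 1.00 |
| 2 | 1.00 | 1.00 | 0.94 | 1.00 |
| 3 | 1.00 | 1.00 | 0.82 | 1.00 |
| 4 | 1.00 | 1.00 | 1.00 | 0.99 |

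With a lag of 1 h or more, all five first-hour draws hold only SA left from the previous dose.

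For comparison, changing the enzyme (ASA half-life 16 v 25 min, no lag) moves R by at most 0.07 at any draw. Moving the lag from 0 to 0.5 h moves the 1 h value by 0.82 − 0.70 = 0.12.

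**4. Share of between-patient variance in the mean post-dose ratio** (half-life CV 15 to 40%).

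| Lag range | From lag | From ASA half-life |
|---|---|---|
| 0.5–2 h or 1–5 h | 78–92% | 2–13% |
| 0–0.5 h | 43–81% | 13–53% |

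**5. Coupling.** With ASA and SA drawn independently with equal log spread, the rank correlation of R is about −0.69 with ASA and +0.69 with SA. With a constant enzyme in the kinetic model, the within-patient correlation of R with ASA is −0.81 (no lag) to −1.00 (lag 1.5 or 3 h).

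**6. The AUC ratio in the same model.**

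AUC_SA/AUC_ASA = ke/[(1−f)·ks] = (SA half-life/ASA half-life)/(1−f) = (3/0.33)/0.5 = 18.2

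Neither lag nor ka appears. Changing ASA half-life from 0.33 to 0.25 h multiplies the ratio by 0.33/0.25 = 1.32. With the enzyme unchanged, SA half-life 2 to 4 h multiplies it by 2/3 = 0.67 to 4/3 = 1.33, and f from 0.3 to 0.7 by 0.5/0.7 = 0.71 to 0.5/0.3 = 1.67.

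**7. How well the draws capture AUC_ASA** (error CV, ka 2/h, lag the only thing varied).

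| Lag (h) | Planned draws | Re-spaced draws |
|---|---|---|
| below 0.5 | 1% | 5% |
| 0.5–2 | 16% | 8% |
| 1–4 | 43% | 15% |
| 2–6 | 100% | 34% |

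For lag 1–4 h, varying ka over 1 to 4/h moves the 43% to between 26% and 62%.

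**8. Detecting a 1.5-fold enzyme change** (simulation with ka, half-lives and f also varying between patients).

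| Lag (h) | Mean ratio, planned draws | Log AUC ratio, re-spaced draws | Gain |
|---|---|---|---|
| 0–0.5 | 0.85 | 1.73 | 2.0-fold |
| 0.5–2 | 0.34 | 1.51 | 4.4-fold |
| 1–4 | 0.33 | 1.21 | 3.7-fold |
| 2–6 | 0.25 | 0.81 | 3.2-fold |

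Entries are standardised effects. With 6 per arm the standard error of a standardised difference is about √(2/6) = 0.58. The ratio's expected signal is therefore 0.25/0.58 = 0.4 to 0.85/0.58 = 1.5 standard errors, and the AUC index's is 0.81/0.58 = 1.4 to 1.73/0.58 = 3.0.

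**The case against.** **The ratio still carries enzyme information.** This stands. A reader might infer that the index measures absorption instead of the enzyme. That goes too far: with lags below 0.5 h and wide enzyme variation, half-life accounts for up to 53% of the variance.

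**Randomisation protects the comparison.** It does so in expectation. A reader might infer that a lag difference will be reported as an enzyme effect. Sample collection has both aspirin-containing arms dosed on an empty stomach on day 10. Only the combination arm has an infusion running, but nothing shown says that this alters absorption. Lost signal is supported; bias is only possible.

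**No regression on ASA or SA is planned.** Correct: the stated analysis is ANOVA between arms. The outcome wording names no analyte and could mean salvianolate, in which case there is no coupling by construction. The sign also depends on the analyte.

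**Samples before release are not undefined.** Under daily dosing, SA left from the previous dose puts the ratio at about 1. It is undefined only if SA is below a quantification limit, which the article does not give.

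**The full plan may define a per-patient summary, and PK-PD modelling is planned.** Possible. But the article itself fixes the ratio as the primary index and as what enters the ANOVA, and a summary of the pointwise ratios inherits their dependence on lag.

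**The AUC ratio has confounders of its own.** This stands. SA elimination and pre-systemic hydrolysis move it as much as a real enzyme change does, and the article's Aspirin section itself mentions hydrolysis in digestive juice.

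**Conclusion.** The point holds in this form: the primary esterase index depends strongly on time since absorption as well as on enzyme activity, and the planned draws leave much of the relevant period thinly covered. The ceiling at 1, the rise with time at a constant enzyme, and the coupling if ASA or SA is the concentration meant need no assumed values. The expected harm is noise and a hidden effect; bias between arms is not shown.

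The size rests on lag and half-life values that the article does not give. Within the ranges tried, the log AUC ratio on re-spaced draws had 2.0 to 4.4 times the standardised effect of the mean ratio on the planned draws. These multiples combine the change of index with the change of draw times and depend on the between-patient spread assumed, so the direction is firmer than the figure. The gain will be smaller for patients already sampled on the planned times. The AUC ratio should be read as overall hydrolysis, not as blood esterase alone.

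**What to change.** 1. **Index.** Make log(AUC_SA/AUC_ASA) per patient on day 10 the primary esterase index, and keep the pointwise ratio as descriptive. Compare the two aspirin-containing arms only, since the salvianolate arm receives no aspirin. This needs no new samples and applies to patients already sampled. Because the trial is open-label and recruiting, record the change before concentrations are reviewed by arm.
2. **Draws.** For patients not yet sampled, move the 5, 30 and 45 min draws to 1.5, 3 and 6 h in all arms, giving 15 min, 1, 1.5, 2, 3, 4, 6, 8, 12 and 24 h. This keeps ten draws and every platelet-marker time in Secondary outcome, and adds one at the planned end of the 1.5 h infusion.
3. **Wording.** State which analyte the blood concentrations in the outcome refer to. If it is ASA or SA, do not relate the ratio to it.
4. **Interpretation.** State that the AUC ratio also reflects SA elimination and pre-systemic hydrolysis.

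**Cost.** An amendment to the sampling times, which also changes the COMT times; less detail early in the infusion; mixed schedules across patients; and slightly worse AUC_ASA precision if lag is under about 0.5 h (5% v 1%). For salvianolate, with an assumed half-life of 0.25 to 2 h, AUC bias goes from +2 to +6% to −2 to +4%, and the share of peak captured from 80–95% to 94–98%.
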